**Fig. 1 Fig1:**
[figure not shown]
Study design and flow. *Notes:* MINI = Mini-International Neuropsychiatric Interview. PDD = Persistent depressive disorder. PPEP4All = Patient and Partner Education Program for All Chronic Illnesses. CAU = care as usual

### Assessment and instruments

As mentioned, the measurement timepoints are at 0, 3, 6, and 12 months; the latter two are follow-up measurements. The first measurement is completed within 1 month prior to the start of the treatment. The study is conducted using a Routine Outcome Monitoring (ROM) system, which periodically measures the presence and severity of psychiatric symptoms in patients with a battery of psychometric instruments and thus monitors therapeutic progress [45–47]. To assist in the administration of the ROM measurements, a web-based application called QuestManager is available. At each timepoint, the questionnaires are completed online via QuestManager (see Fig. 2 for the study schedule and overview of the questionnaires). If preferred or necessary (e.g., computer problems), questionnaires may be completed on paper. The participant may choose to complete the questionnaires at the location of their choice: at their home, the mental health clinic, the research center, or by telephone.

**Fig. 2 Fig2:**
[figure not shown]
Standard Protocol Items: Recommendations for Interventional Trials (SPIRIT) schedule of enrollment, interventions, and assessment of the study. Notes: MINI = Mini-International Neuropsychiatric Interview [35, 36]. EQ-5D-5L = EuroQoL-5 with visual analogue scale [40–44]. TiC-P = Trimbos Medical Technology Assessment questionnaire for psychiatric illness-associated costs [45]. IDS-SR = Inventory of Depressive Symptomatology, self-rated [46–48]. SQ-48 = Symptom Questionnaire-48 [49–52]. SRH = self-rated happiness [53–55]. BRSnl = Brief Resilience Scale [56, 57]. B4CZ = Questionnaire on Burden of Chronic Disease for Patients (or Partners) [58, 59]. ^a^The PPEP4All intervention is mainly provided as a group treatment but can also be offered as an individual treatment. ^b^These questionnaires are administered to partners/caregivers in the study

At the first measurement (i.e., 0 months), participant demographics are registered, and the primary and secondary outcome questionnaires are completed. At the second, third, and fourth measurements (i.e., 3, 6, and 12 months), the outcome questionnaires are again completed.

The *primary outcome measures* pertain to quality of life and healthcare costs (see Fig. 2). Quality of life is measured for both patients and partners/caregivers using the EuroQoL-5 (EQ-5D-5L, including the visual analogue scale, 5 items) [48–52]. Using the EQ-5D-5L, we calculate the mean quality-adjusted life years (QALYs) gained, which is used in the cost-effectiveness analysis (CEA; see “Economic evaluation”). Healthcare consumption (such as contact with healthcare professionals, medical costs, and productivity loss) are measured with the Trimbos Medical Technology Assessment questionnaire for psychiatric illness-associated costs (TiC-P; 30 items) [53].

The *secondary outcome measures* are shown in Fig. 2. Symptoms, psychopathology, and well-being, for patients only, are measured using the Inventory of Depressive Symptomatology, Self-Report (IDS-SR; 30 items) [54–56]; the Symptom Questionnaire-48 (SQ-48; 48 items) [57–60]; and the Self-Rated Happiness survey (SRH; 1 item) [61–63], respectively. In addition, mental resilience of patients is measured using the Brief Resilience Scale (BRSnl; 6 items) [64, 65]. The burden of chronic disease for both the patient and partner/caregiver is measured by the Questionnaire on Burden of Chronic Disease for Patients (B4CZ; 20 items), and the Questionnaire on Burden of Chronic Disease for Partners (B4CZ partners; 16 items), respectively [66, 67]. Directly after the final measurement, patients complete an additional evaluation survey pertaining to the following: (1) treatment modality (group or individual treatment), (2) treatment satisfaction, (3) number of therapy sessions, (4) medication changes (yes/no); and (5) PPEP4All treatment adherence.

## Interventions

### Self-management intervention (PPEP4All)

Each of the nine PPEP4All sessions focuses on specific self-management themes, such as psychoeducation about chronic depression, stress-management using cognitive restructuring and relaxation techniques, reactivation with positive activity planning, social skills building, and mobilization of one’s social network. Although the original PPEP4All program had eight sessions, it has been suggested that an extra PPEP4All session may help sustain enhanced quality of life [19]. PPEP4All in this project includes a ninth session focusing on suicidality, dealing with crises, and relapse prevention. Regarding the latter, participants make a recovery or self-care action plan together with the PPEP4All therapist, using the skills and information learned during the program. For an overview of the PPEP4All self-management themes, see Fig. 3.

**Fig. 3 Fig3:**
[figure not shown]
An overview of the self-management themes of the PPEP4All sessions for the patient and the partner/caregiver. *Notes:* PPEP4All = Patient and Partner Education Program for All Chronic Illnesses. Patient and partner/caregiver programs include the same themes with the exception of sessions 5 and 8. Each session has a general structure of discussing previous homework, presenting active information (i.e., the theme), performing an active exercise, then providing homework and a preview of the next session. The trainer is the PPEP4All therapist. ^a^Participants also gain insight by using a body awareness exercise. ^b^In partner/caregiver program, session 5 focuses on caregiver burden and stress (overload) and relevant challenges. ^c^In partner/caregiver program, session 8 focuses on making a self-care plan

The partner/caregiver program (separate partner group) is the same as the patient program with only one difference: session five focuses on dealing with caregiver burden and patient suicidality (see Fig. 3). The patient and partner/caregiver receive PPEP4All workbooks with homework assignments after each session to practice skills and integrate information. Although the original protocol describes a minimum of 5 and a maximum of 10 participants per group [17], we allowed groups to start with as few as 3–4 participants to avoid undue waiting times.

The PPEP4All program is eclectic, including theoretical influences of system theory (“patient system”) [68, 69], cognitive behavioral theory (“(dys) functional cognitions”) [70], social cognitive theory (“self-efficacy”) [71], stress-coping model (“coping strategies”) [72, 73], transtheoretical model (“motivation to change”) [74]; bio-psycho-social model (quality of life) [75–77], and generic model of self-management [78].

At the time of this project, there are other self-management programs available, such as the *Wellness Recovery Action Plan* (WRAP; a self-designed prevention and wellness process, mainly used for severe mental illness) [79, 80]; *Illness Management and Recovery* (IMR; a standardized psychosocial intervention for severe mental illness like schizophrenia) [81]; and *Self-management for Chronic Anxiety and Depression* (SemCAD; for chronic depressive and anxiety disorders) [82–84]. PPEP4All, however, has advantages when compared to these other interventions. First, PPEP4All involves and engages the partner/caregiver in the treatment process, which has been shown to be effective in reducing the partners’ psychosocial burden concerning the patients’ illness as well as the patients’ outcome [17–21]. A key feature of PPEP4All is that the patient and partner/caregiver receive separate sessions. Maintaining separate sessions allows both patient and partner/caregiver to speak freely about their personal situations. Second, the program can be offered as a group or individual intervention. The treatment modality is determined by the patient and his or her therapist in a process of shared decision making. Third, patients with depression often have comorbid psychiatric or somatic disorders [14, 85]; the PPEP4All program provides a general toolkit with which all these issues can be addressed. Fourth, compared to the other self-management programs, each session of PPEP4All is highly structured, with both patients and partner/caregivers working according to their PPEP4All workbook.

The clinicians of the participating mental health clinics who administer the program are called PPEP4All therapists. Each therapist receives a treatment manual and completes a 3-day certified course with the PPEP4All founder [17, 18, 31, 32, 86, 87]. The training combines homework/self-study with lectures, assignments, group discussions, role play, and self-assessment. The 34 PPEP4All therapists in this project are mainly psychiatric nurses or psychiatric nurse specialists and three are psychologists. After completing their PPEP4All training, all PPEP4All therapists in this study could receive continuous support with regular booster sessions, intervision, consultation with the PPEP4All founder, and an annual national PPEP4ALL symposium.

### Care as usual (CAU)

To compare PPEP4All with what is currently being offered in mental health clinics, the participants randomized to the control group receive care as usual (CAU), thus increasing the ecological validity of the present study. This standard treatment for patients with PDD concerns mostly long-term, non-protocolized supportive care from a psychiatric nurse, with pharmacological maintenance therapy from a psychiatrist. CAU mostly has an individual treatment modality and does not include the partner/caregiver of the patient. Patients allocated to CAU in this study generally continue the standard treatment with their own therapist.

## Treatment integrity

To evaluate the treatment integrity of PPEP4All, each PPEP4All therapist completes a therapy protocol checklist at the end of each group or individual session. On this protocol checklist, the PPEP4All therapist indicates whether and how the provided treatment deviated from the treatment protocol (e.g., the themes mentioned in Fig. 3). It is not possible to record therapy sessions with a video or audio recorder in participating mental health clinics due to privacy law and regulations. Morever, participant attendance is recorded on a separate attendance list and provided to the researchers by the PPEP4All therapist. For CAU, without a specific treatment protocol, we cannot assess its treatment integrity. However, after the final fourth measurement, we collect information about treatment type and modality within CAU, including treatment satisfaction and general medication changes during the course of the research project.

## Sample size and power calculation

We based our sample size on the effect size of previously conducted randomized controlled trials that evaluated relevant interventions in a similar setting in patients with chronic or treatment-resistant depression and that reported a quality of life outcome measure [83, 84, 88–90]. We can expect an effect size around 0.35 [90]. Considering a power level of 80%, alpha of 95%, and equal allocation ratio, we would require 81 participants per group [91–95]. With an additional 16 persons to account for an expected attrition of 10% [96], we expect to include a total sample of 178 participants (2 × 89).

## Data analyses

In this project, we examine both quantitative and qualitative data.

### Quantitative data

Using the data collected from the questionnaires, we examine the clinical and economic effectiveness of PPEP4All (in collaboration with the LUMC Department of Medical Decision Making). This is further specified below.

### Clinical effectiveness

The mean quality-adjusted life years (QALYs) are estimated using EQ-5D-5L data from four assessments. For the *primary data analysis*, we perform an analysis of covariance for the QALY’s using the post-test EQ-5D-5L results with the pre-test scores as covariate [92–94]. In this way, we test whether there is a difference between PPEP4All and CAU, accounting for the variation where the patients started at the first measurement. For the *secondary data analyses*, secondary parameters are tested using weighted generalized estimating equation (GEE) analyses [97, 98]. Clinical effectiveness analyses are examined using superiority testing.

Moreover, we examine tailored care by further investigating for which groups PPEP4All is the most effective. If possible, subgroup analyses are performed for age, gender, ethnicity, and intervention modality (group/individual). In this context, we explore relevant socio-demographics (e.g., education, living situation, and work) and clinical variables (e.g., comorbidity, baseline severity of disease).

For all outcome analyses, an intention-to-treat (ITT) approach is used, according to the CONSORT statement [99]. Analyses are conducted in SPSS, Stata or R.

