## Background

Approximately 10–17% of persons with major depressive disorder (MDD) suffer a chronic course, or a continuous period of at least 2 years [1]. Two types of depressive disorders have a prolonged duration: chronic major depressive disorder and dysthymic disorder [2]. These were combined into one syndrome, persistent depressive disorder (PDD), in the latest Diagnostic and Statistical Manual of Mental Disorders (DSM-5) [3]. Compared to less persistent forms of depression, PDD has a 3–6% lifetime prevalence [3–7] and adverse consequences for patients, such as impaired functioning in social and family relationships, high disease burden for both patient and partner/caregiver, reduced performance in work, comorbid psychiatric and somatic problems, and an increased suicide risk [8, 9].

Many patients with PDD remain in specialized outpatient care without achieving remission, even after having been treated according to the international multidisciplinary depression guidelines [4, 10–12]. Clinicians are resigned to providing long-term supportive non-specific treatment (i.e., care as usual), due to the considerable suffering of patients and the absence of alternative treatment options [13]. More intensive prolonged care, however, often fails to improve therapeutic response; previous research has shown that patients with increasing depression symptom levels have a poor treatment prognosis despite receiving more intensive care [14–16]. The ongoing unsuccessful treatment leaves both patients and clinicians feeling powerless and frustrated [13]. Moreover, this treatment often disregards the partner/caregiver of the patient, although involvement of the partner/caregiver has been shown to be beneficial in improving treatment results of the patient and reducing the partner’s psychosocial burden concerning patient’s disease [17–21].

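### The primary ANCOVA is valid, but pre-specifying the month-0 IDS-SR total as a second covariate would be a nearly free improvement, of small and possibly nil size

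*Protocol article*

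**What the plan says.** In the protocol article, Data analyses, Clinical effectiveness, the primary analysis is an ANCOVA for the QALY that draws on the post-test EQ-5D-5L, "with the pre-test scores as covariate". No second covariate is named.

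Assessment and instruments lists the 30-item IDS-SR among the secondary outcomes for patients. It states that at month 0 "participant demographics are registered, and the primary and secondary outcome questionnaires are completed", so a baseline IDS-SR total is planned for every patient.

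Two other places touch on severity:
- The Background reports earlier research in which "patients with increasing depression symptom levels have a poor treatment prognosis despite receiving more intensive care".
- Clinical effectiveness names "clinical variables (e.g., comorbidity, baseline severity of disease" among the variables to explore when asking which patients benefit most from PPEP4All.

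Sample size and power calculation says "We can expect an effect size around 0.35" and arrives at 81 per group, 162 in all before attrition.

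**The concern.** In a randomised comparison, a baseline covariate that predicts the outcome lowers the residual variance of the treatment contrast and corrects for chance imbalance in that covariate. Randomisation is stratified by gender and research center only, so nothing in the design balances depression severity. The primary model adjusts for severity only as far as the five-item EQ-5D-5L captures it. Eligibility is broad: recurrent or chronic depression, PDD and bipolar II disorder are all admitted, so severity may vary widely.

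If baseline IDS-SR carries prognostic information beyond baseline EQ-5D-5L, the plan leaves some precision unused although the measurement is already being made. What is at stake is the width of the confidence interval for the primary contrast, not its validity.

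**Working it through.** **Step 1: the plan's own figure.** Inputs from Sample size and power calculation: d = 0.35, power 80%, alpha read as 0.05, 1:1 allocation. Without covariate adjustment, two-sided:

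n per group = 2 × ((1.960 + 0.842)/0.35)² = 128.1, so 129.

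The stated 81 is not reproduced. Power at 81 per group is 60.5%. A one-sided test needs 101 per group and has 72.0% power at 81. With an ANCOVA gain, n is multiplied by (1 − r²), so 81 two-sided requires r = √(1 − 81/128.1) = 0.607. The article states no such correlation. The value 0.61 is used below only because it is the one under which 81 per group would be adequate.

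**Step 2: what a second covariate adds.** Write, in absolute value:
- ry = correlation of QALY with baseline EQ-5D-5L (assumed 0.61)
- ri = correlation of QALY with baseline IDS-SR (assumed 0.4 to 0.6)
- re = correlation between the two baselines (assumed 0.5 to 0.7)

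Residual variance, as a share of outcome variance, is 1 − ry² with EQ-5D-5L alone and 1 − R² with both, where

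R² = (ry² + ri² − 2·ry·ri·re)/(1 − re²).

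The relative fall in residual variance equals the squared partial correlation of QALY with IDS-SR given EQ-5D-5L.

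**Step 3: middle values (ri = 0.5, re = 0.6).**
- EQ-5D-5L alone: 1 − 0.3721 = 0.628.
- Both: R² = (0.3721 + 0.25 − 0.366)/0.64 = 0.400, so the residual is 0.600.
- Fall: 1 − 0.600/0.628 = 4.5%; partial correlation √0.045 ≈ 0.21.
- Patient equivalent: 162 × (0.6279/0.5998 − 1) ≈ 7.6, about 8.

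**Step 4: ends of the range.**

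| ri | re | Residual, both | Fall | Patients of 162 |
|---|---|---|---|---|
| 0.427 | 0.7 | 0.628 | 0% | 0 |
| 0.4 | 0.7 | 0.626 | 0.2% | 0.4 |
| 0.5 | 0.6 | 0.600 | 4.5% | 8 |
| 0.6 | 0.5 | 0.512 | 18.5% | 37 |

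The gain is exactly zero whenever ri = ry × re. At re = 0.7 that is 0.61 × 0.7 = 0.427, inside the assumed range, so the lower limit is 0%.

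**Step 5: power at 81 per group, two-sided, with r = 0.607.**

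| Partial correlation of IDS-SR | SE multiplier | Power |
|---|---|---|
| 0 | 1.000 | 80.0% |
| 0.1 | 0.995 | 80.4% |
| 0.2 | 0.980 | 81.6% |
| 0.3 | 0.954 | 83.6% |
| 0.4 | 0.917 | 86.4% |

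The middle case (about 0.21) is worth roughly 2 points of power. The cost is one degree of freedom: 162 − 3 = 159 residual with one covariate, 158 with two.

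**The case against.** The strongest reply is that nothing here is wrong. An ANCOVA adjusted for the baseline of the outcome measure is standard, and the article explains why it adjusts. Baseline EQ-5D-5L is the most natural covariate, all the more so because the QALY is an area under the curve over four assessments that include month 0. A longer covariate list may also stand in a full protocol or SAP that is not shown. All of this stands, and it is why the point is an optional improvement only.

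A reader might infer that the trial itself establishes baseline IDS-SR as prognostic. It does not. The Background sentence concerns rising symptom levels under treatment, not a month-0 score, and mentions neither IDS-SR nor QALYs. Baseline severity appears in the analysis section as something to explore for who benefits most, which is effect modification rather than prognosis.

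The size of the gain is also open to attack. Every correlation is assumed. At the 0.2% corner the partial correlation changes sign, so that worse depression would go with a better QALY at a given EQ-5D-5L; this is hardly a realistic source of precision. The 18.5% corner needs IDS-SR to predict the QALY almost as well as baseline EQ-5D-5L does (0.60 against 0.61) while correlating only 0.5 with it. That is optimistic.

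Finally, the wording on the primary analysis mentions both the QALY and the post-test EQ-5D-5L results. The calculation reads the QALY as the outcome; with another outcome the correlations would differ.

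None of these objections makes the addition harmful.

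**Conclusion.** The primary ANCOVA is sound as written. Adding the month-0 IDS-SR total as a pre-specified covariate is a cheap improvement whose benefit is unknown from the article: between nil and about 18.5% of residual variance under the assumed correlations, about 4.5% at mid-range (about 8 of 162 patients, roughly 2 points of power). The upper end should not be expected.

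Two stronger readings are tempting and not supported. One is that the plan demonstrably loses precision: the article has no figure for what IDS-SR adds beyond EQ-5D-5L, and that addition may be zero. The other is that the extra covariate would make good the sample size. The stated inputs give 129 per group two-sided or 101 one-sided without adjustment, against 81 planned. How 81 was derived is a separate question, and a gain of a few per cent in variance does not answer it.

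**What to change.** In Clinical effectiveness, and in the SAP if there is one, specify the primary model before unblinding as an ANCOVA of the QALY on treatment group, with the month-0 EQ-5D-5L score and the month-0 IDS-SR total as covariates. State that a missing month-0 IDS-SR does not remove a patient from the intention-to-treat analysis.

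The cost is a few words of text and one degree of freedom, with no new data. Timing matters: at the article's date recruitment was still open and data analysts are to be blind to allocation, so the choice can still be made without knowledge of results. Made after unblinding, the same adjustment would be post hoc.

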### Recruitment, enrollment, and allocation

Psychiatric nurses and psychiatrists of the participating mental healthcare locations identify patients eligible for participation according to the above inclusion/exclusion criteria, and they introduce research participation and provide information letters. Patients who are interested and consent to participate in the study sign an informed consent form, which is then sent to the primary research center (LUMC). On this informed consent form, participants also indicate whether they want to be invited to a follow-up nested qualitative interview study in which we evaluate their satisfaction with PPEP4All and their process of implementing coping strategies for chronic depression (see section “Qualitative data”).

To check the inclusion and exclusion criteria formally, a trained research assistant checks the DSM-IV depressive disorders with the Dutch translation of the Mini-International Neuropsychiatric Interview (MINI interview, modules A, B, and C regarding depression, dysthymia, and suicidality). The MINI interview is a well-validated diagnostic interview used to identify psychiatric disorders, with excellent interrater and test-retest reliability [43, 44].

Allocation of participants is performed by an independent data coordinator/data manager, who is not involved in the data collection/analysis (GC; see Acknowledgements). Participants are allocated to either PPEP4All or CAU, using a stratified randomization schedule (stratified by gender and research center) designed by an independent statistician of the Department of Medical Statistics and Bioinformatics of the LUMC.

For the patients allocated to PPEP4All, their main caregiver (e.g., partner, close family member, or close friend) is invited to participate in the project. The data manager makes an appointment with the partner/caregiver, and they sign an informed consent before the first measurement. All participants are informed that participation is voluntary and that they can withdraw from the study at any time without consequences. Participants receive a 20-euro gift card to thank them for their efforts. An overview of the study design and patient flow is provided in Fig. 1.

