### Challenges concerning trial recruitment and implementation

We wish to report some early challenges we faced in the recruitment of participants and implementation of our study design and PPEP4All in the participating research centers. After all, patient recruitment is a key determinant of success or failure for clinical trials [127–129].

Firstly, we learned that recruiting only patients with a primary diagnosis of chronic depression/PDD limited our ability to also recruit potential participants with secondary, or comorbid, PDD (e.g., bipolar disorder type II participants with comorbid PDD). After careful deliberation, we allowed these participants to enroll in our study considering that PPEP4All is a generic self-management program that could potentially be used for a wide range of psychiatric disorders and its focus is on recovery, stabilization, and reintegration into the community [130].

Secondly, we had to make the following adjustments to reduce participant drop-out [93]. Initially, we had proposed providing PPEP4All as group treatment, because a group could be the most cost-effective and efficient modality for mental healthcare. However, several patients with PDD preferred individual PPEP4All and therefore refused to participate. This possible preference for individual PPEP4All was also reported to us by the Client Council of the participating centers. For this reason, although PPEP4All is still primarily offered as a group treatment, we also allow the option to provide PPEP4All as an individual treatment (same protocol). In addition, for patients with a preference for group PPEP4All, we lowered the minimum threshold of required group participants to three rather than the original five, which allowed us to start PPEP4All groups without a long waiting period. Moreover, some patients who explicitly wanted PPEP4All withdrew their study participation after they were randomized to CAU. We remedied this with the message that, if necessary, these patients could receive PPEP4All after CAU and completing at least their first or second follow-up.

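### Group or individual delivery of PPEP4All is a non-randomized choice with no matching split in CAU, so it cannot serve as a treatment-effect subgroup

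*Protocol article*

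**What the plan says.** The Clinical effectiveness section gives the aim of these analyses: "we examine tailored care by further investigating for which groups PPEP4All is the most effective". It then lists the factors: "subgroup analyses are performed for age, gender, ethnicity, and intervention modality (group/individual". The list is conditional on feasibility, and no model or contrast is given for modality.

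Other sections describe what modality is in this trial:

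- **Who sets it.** Self-management intervention (PPEP4All): "The treatment modality is determined by the patient and his or her therapist in a process of shared decision making".
- **Why there are two formats.** Challenges concerning trial recruitment and implementation reports that the initial plan was group treatment, that "several patients with PDD preferred individual PPEP4All and therefore refused to participate", and that now, "although PPEP4All is still primarily offered as a group treatment, we also allow the option to provide PPEP4All as an individual treatment".
- **What is randomized.** Recruitment, enrollment, and allocation: "Participants are allocated to either PPEP4All or CAU, using a stratified randomization schedule (stratified by gender and research center". Neither modality nor preferred modality is a factor.
- **The control arm.** Care as usual (CAU): "CAU mostly has an individual treatment modality and does not include the partner/caregiver of the patient".
- **When it is recorded.** Assessment and instruments puts the modality item in a survey completed straight after the final measurement. Treatment integrity says that type and modality of treatment within CAU are collected after the fourth measurement.

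**The concern.** Age, gender and ethnicity are patient characteristics that allocation cannot alter. PPEP4All and CAU patients can be compared within each level of them, and randomization protects the comparison. Modality does not have this property. It describes how one of the two treatments was delivered, and patient and therapist decided it together. Patients who choose a group may differ from those who choose individual sessions in preference, severity or comorbidity, or in their therapist's judgement of them.

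The stated purpose is tailored care. Listed beside three legitimate factors, a difference by modality would naturally be read as evidence that one format works better, when the design cannot separate the format from the patients who chose it.

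**Working it through.** **Step 1. Is there a randomized contrast by modality?** There are three ways to carry out the listed analysis.

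| Contrast | What is compared | Protected by randomization? |
|---|---|---|
| Group PPEP4All vs individual PPEP4All | Two self-selected parts of one arm | No |
| Each PPEP4All format vs all of CAU | A self-selected part of one arm vs the whole of the other | No |
| PPEP4All vs CAU within recorded modality | Format of PPEP4All matched to format of CAU | No: a different treatment, mostly individual, recorded after follow-up |

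A valid version would need preferred modality recorded before allocation in both arms. The article describes no such record.

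**Step 2. How large could the error be?** The document gives no figure for the bias and none for the split between formats, so there is nothing to reproduce. The following is an illustration.

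Inputs from Sample size and power calculation: planning effect 0.35; 81 patients per arm.

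Assumptions, not document figures:
- The true effect is 0.35 SD in both formats, so the true modality difference is zero.
- The outcome has SD 1 in the analysis.
- Those who choose group have a better prognosis by *g* SD *after* baseline adjustment, with *g* from 0.1 to 0.5. The direction is arbitrary.
- The share *s* choosing group is 0.5 (40 and 41 patients) or 0.7 (57 and 24).

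Formulas:
- Apparent effect of group vs all CAU = 0.35 + *g*(1 − *s*)
- Apparent effect of individual vs all CAU = 0.35 − *g s*
- Apparent modality difference = *g*, whatever *s* is
- SE of the within-arm difference = √(1/n_group + 1/n_individual): √(1/40 + 1/41) = 0.222 and √(1/57 + 1/24) = 0.243
- Chance of p < 0.05 (two-sided) = 1 − Φ(1.96 − *g*/SE) + Φ(−1.96 − *g*/SE)

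| *g* (SD) | *g*/0.35 | *s* | Group vs CAU | Individual vs CAU | Chance of a false modality difference |
|---|---|---|---|---|---|
| 0.1 | 29% | 0.5 | 0.40 | 0.30 | 7% |
| 0.1 | 29% | 0.7 | 0.38 | 0.28 | 7% |
| 0.2 | 57% | 0.5 | 0.45 | 0.25 | 15% |
| 0.2 | 57% | 0.7 | 0.41 | 0.21 | 13% |
| 0.35 | 100% | 0.5 | 0.525 | 0.175 | 35% |
| 0.35 | 100% | 0.7 | 0.455 | 0.105 | 30% |
| 0.5 | 143% | 0.5 | 0.60 | 0.10 | 61% |
| 0.5 | 143% | 0.7 | 0.50 | 0.00 | 54% |

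With no residual gap, the chance of a false difference is 5%. The table shows only how an assumed gap carries through. It does not estimate the gap.

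**The case against.** The strongest reply is that this is a conditional, exploratory addition. No model or decision rule is tied to it, and a baseline-adjusted within-arm description would not be excluded by the sentence. Such detail is often left to an analysis plan, which is not at hand. The primary model is an analysis of covariance on the pre-test score, and the same section names comorbidity and baseline severity for exploration, so part of any selection could be adjusted away.

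Much of this stands. It limits the weight of the point, and it is why the gap above is defined as what remains after adjustment. It does not remove the point. The article does more than leave detail open: it names modality as a factor for finding where PPEP4All is most effective. Adjustment for measured severity also cannot be relied on to remove patient preference or therapist judgement.

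Some stronger readings are tempting but not supported:

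- **That format depends on whether a group could be filled.** The article says the minimum group size was lowered to avoid long waits. It does not say that unfilled groups were switched to individual sessions.
- **That CAU patients could never have stated a modality preference.** The timing of the choice is not given, and some patients voiced a preference at recruitment. What can be said is that no recording in both arms is described.
- **That the modality result drives the economic evaluation.** The article remarks that group delivery could be the more cost-effective format, but neither the cost-effectiveness analysis nor the budget impact scenarios are split by modality.

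**Conclusion.** The point holds for modality only, and as a matter of design. No randomized modality-specific contrast is available, so the listed analysis would give a confounded answer to the question it is meant to serve. This rests on the article's account of who chooses modality, what is randomized, and what is recorded in CAU and when.

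The size of the bias is unknown. Under the assumed residual gap of 0.1 to 0.5 SD, the false modality difference is between 29% and 143% of the planning effect; those percentages are only as good as the assumption.

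A reader might infer that the main result is at risk. It is not: PPEP4All versus CAU as randomized does not depend on this analysis. Nor does the point touch the age, gender or ethnicity subgroups. It is worth correcting before analysis, but it does not threaten the trial.

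**What to change.** In Clinical effectiveness, remove intervention modality from the list of treatment-effect subgroups. Add one sentence saying that group and individual PPEP4All will be compared within the PPEP4All arm as a non-randomized, exploratory description adjusted for baseline variables, with no claim that one format is more effective.

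This costs one sentence and calls for no new data. The trial gives up a claim about which format works better, which its design cannot support.

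Asking for preferred modality before allocation in both arms would in principle allow a valid subgroup. It is not a practical remedy here: under Trial status, recruitment began on 1 April 2017 and was due to end on 1 April 2021, two months after the protocol version dated 1 February 2021, so few patients would be left to ask.
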